**List of Abbreviations:**

|               |                                                                      |
|---------------|----------------------------------------------------------------------|
| AUC           | Internal cross-validated area under the curve                        |
| CHADS2 Score  | Congestive heart failure, High blood pressure, Age, Diabetes, Stroke |
| CPR           | Clinical prediction rules                                            |
| CURB-65 Score | Confusion, Urea, Respiratory rate, Blood pressure, age 65 or older   |
| CVD           | Center for Vaccine Development                                       |
| DEP           | Diarrhoea Etiology Prediction algorithm                              |
| DSMP          | Data and Safety Monitoring Plan                                      |
| GEMS          | Global Enteric Multicenter Study                                     |
| HIPAA         | Health Insurance Portability and Accountability Act                  |
| LMICS         | Lower- and middle-income countries                                   |
| MUAC          | Mid-Upper Arm Circumference                                          |
| NSTEMI        | Non-ST-elevation Myocardial Infarction                               |
| PHI           | Protected Health Information                                         |
| PPC           | Parent or primary caretaker                                          |
| SAE           | Serious Adverse Event                                                |
| TAC           | TaqMan Array Card                                                    |
| TIMI Score    | Thrombolysis In Myocardial Infarction                                |
| VIDA          | Vaccine Impact on Diarrhea in Africa                                 |
| WHO           | World Health Organization                                            |

## Project Summary

**Research Protocol Title:** The acceptability and impact of Diarrheal Etiology Prediction (DEP) algorithm among physicians treating children with diarrhea

### Background (brief):

#### a. Burden:

Diarrhoeal diseases are a leading cause of morbidity and mortality in children worldwide, with an estimated one billion cases and 500,000 deaths annually. While the majority of deaths due to diarrhoea occur in lower-income countries, infectious diarrhoea remains a significant problem in high-income countries. Accurate and cost-effective determination of diarrhoea etiology is important for proper case management in children and for public health.

#### b. Knowledge gap:

Clinical prediction rules (CPRs) help clinicians interpret clinical information and can improve decision making. A recent systematic review showed that out of 137 studies of conditions for which clinical prediction rules have been developed for children, only 2 were for diarrhoea, both of which are for the assessment of dehydration. Similarly, the majority of available guidelines for pediatric diarrhoea are focused on the route, timing, and choice of fluids for rehydration. However, these studies were limited by low rates of pathogen identification, small sample sizes, use of a single study site, and suboptimal prediction performance. Better tools for decision making about the diarrhea etiology and evidence-based guidelines regarding use of antibiotics and laboratory testing in children with diarrhoea are clearly needed.

#### c. Relevance:

The majority of decisions for use of antibiotics in diarrhoeal illnesses are made empirically. In lower and middle-income countries (LMICs), due to cost constraints, etiological diagnosis is rarely made, and a large number (up to 70%) of patients with acute diarrhoea are prescribed antibiotics. In both high and low resource settings, inappropriate use of antimicrobials leads to unnecessary toxicity for the individual, increased costs and an increase in antibiotic resistance in the community. Thus, methods for guiding appropriate use of antibiotics for pediatric diarrhoea in both high- and low-resource settings are urgently needed.

Clinical prediction rules (CPRs) are decision-making rubrics that help clinicians estimate the likelihood of a patient outcome. Clinical prediction rules integrated into clinical decision making have the ability to direct clinicians towards more evidence-based behaviors, resulting in improved care and reduction of costs and have the potential to help healthcare workers worldwide address clinical uncertainty and provide improved care for children with diarrhoea.

**Hypothesis:** We hypothesize that Diarrheal Etiology Prediction (DEP) algorithm for calculating probability of viral etiology of diarrhea will safely reduce inappropriate antibiotic use among children <5 years old with acute diarrhea.

**Objectives:** To examine the acceptability and impact of a Diarrheal Etiology Prediction (DEP) algorithm among physicians treating children with diarrhea.

**Methods:** This is a randomized crossover study and clinicians will be randomized to periods where they will use a rehydration calculator application with or without the DEP. The crossover will include a washout period to reduce carryover effect. The study will be conducted over a 9-weeks period. We will use a random number generator to randomize clinicians to DEP or control arm for the first 4 weeks. After the first 4 weeks, there will be a 1-week washout period without decision-support, after which each clinician will cross-over to the other arm for the next 4 weeks.

### Outcome measures/variables:

The primary outcome is the proportion of children given antibiotic prescriptions, as assessed by hospital records. Secondary outcomes are the proportion of children with resolution of diarrheal symptoms at 10-days after enrollment, and clinician satisfaction towards use of the DEP, as assessed by pre- and post-study questionnaires

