## Description of the Research Project

**Hypothesis to be tested:** We hypothesize that Diarrheal Etiology Prediction (DEP) algorithm for calculating probability of viral etiology of diarrhea will safely reduce inappropriate antibiotic use among children <5 years old with acute diarrhea.

**Primary objective:** To examine the acceptability and impact of a Diarrheal Etiology Prediction (DEP) among physicians treating children with diarrhea.

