#### Enrolment and consent of patients

Study staff will be situated in the intake areas and will identify children 2–59 months with diarrhoeal illness. Study staff will select consecutive subjects between 8am and 2pm on weekdays for enrolment on arrival to the Hospital. Potential participants' information (age and time of intake, etc) will be recorded in a screening log. Study staff and nurses will inform parents or primary caretakers (PPC) of patients who meet the inclusion/exclusion criteria about the study. If PPC is interested in the study, study staff will determine if the child is eligible and then provide more detailed information to the PPC's of eligible subjects. Detailed information will be provided in French and will include goals, risks, and benefits of the study. Once the PPC exhibits understanding, written consent will be obtained in the local language prior to enrolling the subject in the study. Illiterate PPC's will give consent by marking the consent form with their thumbprint or signature after a study staff member reads the consent form in French. Children without a PPC present will be excluded from the study. The last signature on the consent will be from the enrolling staff member.

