#### c.iii. Data collection

**Clinicians:** We will use a screening form (Appendix 3) and questionnaire (Pre- and post-Study) to collect quantitative (Appendix 4 & 5) data regarding clinician attitudes and experiences using the App and its role in diarrheal management. These questionnaires will be administered by study coordinators at 2 time points: 1) at the start of the study, and 2) at the end of the study. We will also use the App itself to collect data regarding physician usage.

**Children:** For each enrolled patient, study staff will collect:

- At enrolment, demographic and clinical variables
- At discharge, hospital outcome measures, including intravenous and oral fluids, and antibiotics, zinc administered
- At 10-days post-discharge, health outcomes including persistence of diarrheal and abdominal symptoms, returns to healthcare, and medication use since discharge, will be collected over a phone call.

**Instruments:** As mentioned, electronic tools that are compliant to the protections of PHI (Protected Health Information) will be used in this study. These include the Outbreak Responder software, which includes the DEP, and if needed, RedCap.

**Data Storage:** Data collected on Outbreak Responder software will be stored on a secure cloud-based server (server is physically based in Singapore; this is a HIPAA compliant server managed by Amazon Web Services).

Access to the server(s) will be restricted and the server management conforms to industry standard for health information.

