### **Data Analysis**

The primary endpoint of estimating the proportion difference of children given antibiotic prescriptions in the control versus the DEP arms can be analyzed using a generalized linear mixed model (GLMM). The response is binary (yes or no), and we will treat provider and clinic as random, while accounting for the time period in order to estimate the treatment effect. All data analyses will be conducted in R. For the physician satisfaction end point, we will use characteristic tables to summarize the results of the survey.

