### **Definitions of Serious Adverse Events (SAE) and Adverse Events:**

**Serious Adverse Event:** Any adverse event that results any of the following outcomes: death, significant disability/incapacity, and/or life-threatening situation of any patient within the study period (enrolment of patient at admission to 10 days after discharge).

**Adverse Events:** An adverse event will be defined as an untoward medical event temporally associated with a medical intervention in a patient that does not necessarily have a causal relationship with the treatment.

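### The day-10 symptom-resolution outcome is counted from enrolment but collected 10 days after discharge, so for any child who stays it is not observed on its defined day

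*Protocol*

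**What the plan says.** Under Outcome measures/variables, the protocol lists as a secondary outcome "the proportion of children with resolution of diarrheal symptoms at 10-days after enrollment". The clock starts early: under Enrolment and consent of patients, consecutive children are selected "for enrolment on arrival to the Hospital".

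The Data collection section (c.iii) lists three data points per child: enrolment, discharge and one follow-up phone call. The discharge item is "At discharge, hospital outcome measures, including intravenous and oral fluids, and antibiotics, zinc administered". The call is where symptom status is obtained: "At 10-days post-discharge, health outcomes including persistence of diarrheal and abdominal symptoms". It also covers returns to care and medication since discharge.

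The serious adverse event definition uses the discharge anchor too. Its study period is "enrolment of patient at admission to 10 days after discharge".

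Nowhere does the protocol schedule a contact on day 10 counted from enrolment, and nowhere does it say that the date of resolution is recorded.

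**The concern.** The outcome is defined on one time scale and measured on another. A statistical analysis plan cannot repair this, because it cannot recover an observation that the schedule does not make. Left alone, the reported proportion would carry a day-10 label while mixing children assessed on different days.

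The choice of anchor also matters for the comparison. Enrolment on arrival is not affected by what the clinician then does with the application. Discharge follows the intervention and may depend on it. A call timed from discharge can therefore reach children in the two conditions at different times since enrolment, even though both follow the same calling rule. Time since enrolment bears directly on whether acute diarrhoea has resolved, so a difference in assessment time could appear as a difference in recovery, or conceal one.

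**Working it through.** The check is one of timing. The protocol states no figure for this outcome that could be reproduced.

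**Inputs**
- Start of clock: arrival, day 0 (Enrolment and consent of patients).
- Defined assessment: day 10 after enrolment (Outcome measures/variables).
- Actual contact: 10 days after discharge (Data collection, c.iii).
- End of the serious adverse event window: 10 days after discharge (serious adverse event definition).
- Length of stay L, in days from enrolment to discharge: not given. A range of 0 to 5 days is assumed for illustration.
- Share of children who stay: not given. Stays are foreseen, since the clinical setting covers severe dehydration and intravenous fluids, and the adverse event definition refers to admission.

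**Step 1: when the call falls.** Discharge is on day L, so the call is on day L + 10, and its distance from the defined day is (L + 10) − 10 = L.

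| L (assumed) | Day of call after enrolment | Days past the defined day |
|---|---|---|
| 0 | 10 | 0 |
| 1 | 11 | 1 |
| 3 | 13 | 3 |
| 5 | 15 | 5 |

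The definitions coincide only at L = 0.

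**Step 2: what the call can say about day 10.** A child whose diarrhoea stopped between day 10 and day 10+L was unresolved on the defined day but is recorded as resolved. A child who was well on day 10 and relapsed before the call is recorded as unresolved. Current status at the call identifies neither; a date of resolution would identify the first.

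**Step 3: between conditions.** The difference in mean assessment time is (10 + mean L with the prediction algorithm) − (10 + mean L in control), which is the difference in mean length of stay. It is zero only if mean stay is the same in both conditions.

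**Step 4: can the sign be fixed?** Two mechanisms are plausible, and they oppose each other.
- If antibiotic treatment prolongs stay, control children are assessed later, because the sample size section expects 90% treated in control against 80% with the algorithm. Extra time then favours control.
- If children recover more slowly without antibiotics and stay longer for that reason, the algorithm condition is assessed later. Extra time then favours the algorithm.

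The documents give nothing with which to weigh one against the other.

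**The case against.** The best defence is that the mismatch may be small. The clinical setting is uncomplicated diarrhoea and includes children without dehydration, the staff training text describes the call as following a visit, and same-day discharges are unaffected. This stands as a limit on size: without the admitted share or length of stay, nobody can say how many children are affected. It does not remove the contradiction.

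A second defence is that the child follow-up form is not shown and may ask when diarrhoea stopped. If so, day-10 status could be derived. That is possible, but the protocol's description of the call mentions persistence and no date, so it should be stated.

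A third is that both conditions share one calling rule and remain comparable. This holds only if length of stay is similar in both, because the rule's anchor comes after the intervention.

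A reader might go further. The hypothesis says that the algorithm "will safely reduce inappropriate antibiotic use among children <5 years old with acute diarrhea", and one could infer that no comparison in this trial could support that word. The documents do not bear this out:
- No section ties the word to symptom resolution. Serious adverse events and returns to care are also collected.
- The planned size does not rule out such a comparison. There are 15 × 12 = 180 children per condition, and the stated correlations give a design effect of 1 + 11 × 0.15 − 12 × 0.15 = 0.85. At an assumed 90% resolution, an illustrative 10-point non-inferiority margin (one-sided 0.025, 80% power) needs 142 × 0.85 = 120.7, or 121 per condition. A 5-point margin would need 482, so the answer depends on the margin.
- The Data Analysis section gives no analysis for symptom resolution, but an analysis or margin for a secondary outcome may sit in a statistical analysis plan that is not at hand. Its absence here is not a finding.

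**Conclusion.** The point holds as an internal contradiction about the timing of one secondary outcome. On the schedule as written, resolution at day 10 after enrolment is observed on its defined day only for children discharged on the day they enrol. For others the call is late by the length of stay: day 10 to 15 if stays run from 0 to 5 days, which is an assumption.

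A differential assessment time between conditions is possible, because discharge follows the intervention, but it is not shown. A reader might infer that the later anchor hides slower recovery under the algorithm. The documents do not support a direction, since the two plausible mechanisms have opposite signs. The primary outcome, antibiotic prescription taken from hospital records, is not touched.

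**What to change.** Use one anchor in Outcome measures/variables and in Data collection (c.iii). Day 10 after enrolment is preferable because the intervention cannot move it. Redefining the outcome to 10 days after discharge would also make the text consistent, but would keep an anchor that the intervention may influence.

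Either of two changes achieves this:
1. Schedule the symptom call on day 10 after enrolment, with a child still admitted on that day assessed on the ward. The cost is a second brief contact for admitted children, because the serious adverse event window would otherwise have no closing contact.
2. Keep the call 10 days after discharge and add a question on the date diarrhoea stopped, so that day-10 status can be derived. The cost is one question and some recall error.

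In both cases leave the serious adverse event window no shorter than it is now. Neither option changes the sample size, the randomisation or the primary analysis.

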## Description of the Research Project

**Hypothesis to be tested:** We hypothesize that Diarrheal Etiology Prediction (DEP) algorithm for calculating probability of viral etiology of diarrhea will safely reduce inappropriate antibiotic use among children <5 years old with acute diarrhea.

**Primary objective:** To examine the acceptability and impact of a Diarrheal Etiology Prediction (DEP) among physicians treating children with diarrhea.

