#### Decision-making for appropriate antibiotic use

The majority of decisions for use of antibiotics in diarrhoeal illnesses are made empirically. In lower- and middle-income countries (LMICs), due to cost constraints, etiological diagnosis is rarely made, and a large number (up to 70%) of patients with acute diarrhoea are prescribed antibiotics. However, in contrast to high resource settings, bacterial pathogens may be very common in low resource settings. In the multicenter Global Enteric Multicenter Study (GEMS) study, we found that detection of *Shigella* ranged from 16-78% of children with dysentery and 2-43% of children with watery diarrhoea. In both high and low resource settings, inappropriate use of antimicrobials leads to unnecessary toxicity for the individual, increased costs and an increase in antibiotic resistance in the community. Thus, methods for guiding appropriate use of antibiotics for pediatric diarrhoea in both high- and low-resource settings are urgently needed.

Clinical prediction rules (CPRs) are decision-making rubrics that help clinicians estimate the likelihood of a patient outcome. A number of prominent prediction scores have been widely adopted for clinical use. Examples include the CHADS2 score for stroke risk in patients with atrial fibrillation, the TIMI score for mortality in patients with NSTEMI, and the CURB-65 Score for mortality in community-acquired pneumonia. Clinical prediction rules integrated into clinical decision-making have the ability to direct clinicians towards more evidence-based behaviors, resulting in improved care and reduction of costs. CPRs can also reduce antimicrobial usage, as shown by the use of scores for strep pharyngitis, and linking CPRs with testing guidance may further reduce antimicrobial usage. Thus, clinical prediction rules have the potential to help healthcare workers worldwide address clinical uncertainty and provide improved care for children with diarrhoea.

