## Research Design and Methods

**Strategic Plan Overview:** This is a randomized crossover study, where clinicians will be randomized to periods where they will use a rehydration calculator application with or without the DEP. The crossover will include a washout period to reduce carryover effect. The study will be conducted over a 9-week period. We will use a random number generator to randomize clinicians to DEP or control arm for the first 4 weeks. After the first 4 weeks, there will be a 1-week washout period without decision support, after which each clinician will cross-over to the other arm for the next 4 weeks.

The DEP algorithm involves entry of clinical variables (age, bloody diarrhea, Breastfeeding, vomiting, mid-upper arm circumference- MUAC). The output provides the probability that the cause of the diarrhea is viral.

The DEP will be integrated as a feature into a Rehydration Calculator application that has previously been tested as part of two clinical studies in Bangladesh (icddr,b/ IEDCR; Khan AI et al, submitted 2019 and Haque et al. PLoS NTD 2017). The Rehydration Calculator with the DEP turned 'off' will serve as a control. The experimental arm of the study will have the DEP turned 'on'. The Rehydration Calculator is an electronic decision-support tool that provides recommendations for rehydration based on entry of age, gender, weight, and dehydration status. Given the outcome measures of this study, the Rehydration Calculator will be configured to not give antibiotic recommendations.

**Study Sites:** 4 Healthcare Facilities in Mali. ( CSRef CV, ASACOSAB1, CSRef CVI, ASACOYIR)

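### The hypothesis concerns inappropriate antibiotic use, but every antibiotic measure counts any prescription, so a positive primary result would show less prescribing overall and not the stated hypothesis

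*Protocol*

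**What the plan says.** **Hypothesis.** In the Project Summary, and again under Description of the Research Project, the DEP "will safely reduce inappropriate antibiotic use among children" below five years of age.

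**Outcomes.** Under Outcome measures/variables: "The primary outcome is the proportion of children given antibiotic prescriptions, as assessed by hospital records". The same section continues: "Secondary outcomes are the proportion of children with resolution of diarrheal symptoms at 10-days after enrollment", together with "clinician satisfaction towards use of the DEP, as assessed by pre- and post-study questionnaires". No outcome classifies a prescription as appropriate or not.

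**Sample size and analysis.** The sample size section plans for 90% of control children and 80% of DEP children receiving antibiotics, without qualification. Data Analysis is framed in the same terms: "The primary endpoint of estimating the proportion difference of children given antibiotic prescriptions in the control versus the DEP arms".

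**What the tool does.** Under Research Design and Methods, clinicians enter "age, bloody diarrhea, Breastfeeding, vomiting, mid-upper arm circumference- MUAC". Then: "The output provides the probability that the cause of the diarrhea is viral". The last paragraph under Decision-making for appropriate antibiotic use adds that the derived rule multiplies odds from the clinical model, from models using local climate and recent clinical trends, and a pre-test odds.

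**Context.** The Background states that too little antimicrobial treatment of some bacterial and protozoal infections can do harm. Shigella detection "ranged from 16-78% of children with dysentery and 2-43% of children with watery diarrhoea". Collaborative Arrangements marks sample collection as not applicable. The data collection section provides for a phone call 10 days after discharge, covering persistent symptoms, returns to healthcare and medication use.

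**The concern.** The tool is meant to discriminate: it should lower prescribing where a viral cause is likely and leave it alone elsewhere. The primary outcome does not observe discrimination. It gives the same credit to every withheld antibiotic, although the protocol itself says underuse can be harmful. It also errs the other way: a tool that lowered prescribing in likely-viral cases and raised it in likely-bacterial ones would be under-credited.

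What is at stake is the conclusion. A report that follows the protocol's wording would claim a reduction in inappropriate use from data that show only a reduction in use.

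**Working it through.** **1. Hypothesis against measures.**

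| Element | Quantity |
|---|---|
| Hypothesis (Project Summary; Description of the Research Project) | inappropriate antibiotic use, reduced safely |
| Primary outcome | any antibiotic prescription |
| Sample size | any antibiotic, 90% vs 80% |
| Primary analysis | difference in any antibiotic prescription |
| Secondary outcomes | symptom resolution; clinician satisfaction |

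Two routes could have defined inappropriate use. Aetiology is closed, because no samples are taken. The WHO guidelines named under Clinical setting govern care, but they are not used to classify prescriptions.

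**2. The plan's own figure.** The protocol states power above 95%. Inputs: 15 clinicians × 12 children = 180 per condition; both correlations 0.15.
- Design effect: 1 + 11 × 0.15 − 12 × 0.15 = 0.85, so effective n = 180/0.85 = 211.8.
- SE = √[(0.90 × 0.10 + 0.80 × 0.20)/211.8] = 0.0344.
- Power = Φ(0.10/0.0344 − 1.96) ≈ 83% (82% with pooled variance).

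The stated figure is not reproduced. That is a separate matter: it concerns the any-antibiotic comparison, and the present point does not depend on it.

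**3. Why the primary result cannot discriminate.** Let s be the share of children with a high viral probability, and let Δ denote the fall in prescribing:

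Δ(overall) = s × Δ(high) + (1 − s) × Δ(low)

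The planned 10 points arise from Δ(high) = 10/s with Δ(low) = 0 (selective), and equally from Δ(high) = Δ(low) = 10 (indiscriminate). The primary estimate is the same for any s. The documents do not give s, and the argument does not need it.

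**4. Could children with bloody stool alone drive the result?** They are not excluded. Their share b is not in the documents, so it is assumed here. Fall needed among them for the whole 10 points = 10/b:

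| Assumed b | Children per condition | Fall needed (points) |
|---|---|---|
| 5% | 9 | 200 (impossible) |
| 10% | 18 | 100 |
| 15% | 27 | 67 |
| 20% | 36 | 50 |
| 25% | 45 | 40 |

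A smaller case: at b = 15%, a fall of one third among them gives 0.15 × 0.333 = 5 points overall, that is 90% vs 85%. Then z = 0.05/√(2 × 0.875 × 0.125/180) = 1.43, or 1.43/√0.85 = 1.56 with the design effect. Neither reaches 1.96.

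**5. Precision of an analysis by viral probability.** For illustration, take two groups, 90% vs 80% in each, and ignore clustering.
- Even split (90 per condition per group): SE of the difference between the two arm effects = √(0.25/90 + 0.25/90) = 0.0745; 95% half-width = 1.96 × 0.0745 = 14.6 points.
- By stool type at an assumed 15% bloody (27 and 153 per condition): √(0.25/27 + 0.25/153) = 0.104; half-width 20.5 points.

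**The case against.** **Harm is watched.** The hypothesis says safely, and symptom resolution, returns to care and later medication use are collected. This stands. A reader might infer that nothing would detect under-treatment, and the protocol does not support that. But these outcomes do not measure appropriateness, and Data Analysis describes no analysis for them.

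**Subgroup and interaction analyses belong in a statistical analysis plan, which is not shown.** True of the analysis detail, and its absence here is not the finding. The finding is that the protocol states a hypothesis which none of its own outcomes measures. A subgroup in another document would not repair that. The outcome, sample size and analysis do agree with one another and fit the broad objective of acceptability and impact; the hypothesis is the part out of line.

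**A fall in bloody cases is unlikely.** A reader might infer that withholding antibiotics in bloody diarrhoea could by itself make the trial positive. The working does not support this. The 5-point case is not significant, the 10-point case needs a very large fall, the share is unknown, and bloody stool is itself an input to the tool.

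**Bloody stool is a poor yardstick.** This also stands. The section on the paucity of decision-making tools says that relying on dysentery missed nearly 90% of shigellosis, and Shigella occurs in watery cases too. The protocol nowhere says that bloody stool defines need. A rule allowing a claim about inappropriate use only when the fall is confined to non-bloody cases would import a criterion the documents do not supply.

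**An analysis by DEP probability is partly circular.** A larger fall at high probability shows that clinicians followed the tool, not that the withheld antibiotics were unnecessary. Agreed, which is why it should be an estimate and not a licence for a claim.

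**Conclusion.** The point holds. The primary comparison is a valid test of overall antibiotic prescribing, but it cannot support a hypothesis about inappropriate use, whatever its result. This follows from the protocol's wording alone and rests on no assumed figure. The bloody-stool shares and the two-group precision figures are illustrations under stated assumptions; they do not show that the trial would be positive for the wrong reason.

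The sponsor should act on this. It affects what may be concluded, not whether the primary analysis is sound.

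**What to change.** 1. Keep the primary outcome. Word the hypothesis and the conclusion as antibiotic prescribing.
2. Prespecify one secondary analysis that estimates the arm difference by DEP viral probability (an arm-by-probability term in the planned mixed model). Report it as an estimate with its confidence interval, not as a condition for any claim. Show results by bloody and non-bloody stool as descriptive support only.
3. Compute the probability offline in the same way for every child in both arms, preferably from what study staff record at enrolment, so that it does not depend on whether the DEP was switched on.
4. Record all five clinical inputs in both arms. Breastfeeding needs checking: the control application is described as using age, gender, weight and dehydration status, and the examples of clinical and biometric data under Individual privacy include bloody stool, vomiting and MUAC but not breastfeeding.
5. Keep visit date, site and any climate, recent-trend and pre-test inputs that the deployed version uses. Without these, the five clinical fields may not reproduce the probability shown to clinicians.

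Cost: some analysis and data-keeping work, and no change to the primary comparison or the sample size. The interaction estimate will be imprecise and should be presented as such.
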